### Measures to minimize bias

The following measures will be taken to minimize bias in this study:Due to the nature of the study interventions, site-specific effects may arise. Consequently, a cluster crossover study design was selected because each study site will administer both study interventions at randomly selected times, thereby allowing for within-site estimates of the intervention effect.The assessment and management approach (FNAST or ESC) used at each study site may substantially affect the outcomes of interest. To address potential confounding, each study site will be required to use the same assessment and management approach for the duration of the study. Additionally, the randomization scheme will be stratified by the assessment and management approach to ensure that the percentage of study sites using each assessment and management approach is similar between the two sequences.

### Analysis plan

All statistical analyses will be performed by DCC biostatisticians. Data will be monitored for accuracy and completeness throughout the study. Analyses will only be performed after the database has been locked.

For descriptive summaries of study data, the following will be presented:Nominal/categorical measures will be summarized using frequencies and percentages.Interval or ratio scale measures will be summarized using means, standard deviations, medians, 95% confidence intervals (CIs), 25th and 75th percentiles, and ranges.Ordinal measures will be summarized depending on the number of levels. An ordinal measure with five levels or fewer will be summarized as a nominal measure. An ordinal measure with more than five levels will be summarized as an interval or ratio scale measure.

Unless otherwise specified, each objective will be addressed by fitting a generalized linear mixed-effects model (GLMM) specified with a distribution and link function appropriate to each participant-level outcome in infants with NOWS who are assessed and managed with FNAST and ESC separately. Each model will also include the following fixed effects:Dosing approach (symptom-based dosing approach or scheduled opioid taper approach)Study period in which participant was born (study period 1 or 2)

Random effects for site will also be included in the model to account for within- and between-period intra-cluster correlation. The form of the random effect for site will be evaluated by comparing information criteria across the models with different forms and selecting the form that produces the best fit. Small sample corrections will also be employed to account for the small number of sites that are randomized.

Because it is of clinical interest to separately evaluate all objectives in infants with NOWS who are assessed and managed with FNAST and ESC separately, no adjustment for multiple comparisons will be made.

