### Stratification, randomization, and blinding/masking

Each study site (i.e., cluster) will be randomized in a 1:1 allocation ratio to one of two sequences, following a 5-week run-in:Scheduled opioid taper approach for 5 months (period 1) followed by a 3-week washout followed by symptom-based dosing approach for 5 months (period 2)Symptom-based dosing approach for 5 months (period 1) followed by a 3-week washout followed by scheduled opioid taper approach for 5 months (period 2)

The randomization scheme will be stratified by the assessment and management approach used at each study site (i.e., FNAST or ESC). Study sites will be notified of their allocated sequence following randomization.

Due to the nature of the study intervention, the protocol study team, site PI, site study team, and participants will be unblinded to the assigned study intervention.

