### Consent or assent

#### Waiver of consent for in-hospital participation

The use of a cluster crossover design for this study will allow for randomization of the study intervention at the level of the study site. Study sites will adhere to their assigned approach for the pharmacologic treatment of all infants with NOWS cared for at their site throughout the study. Maintaining a generalizable study population will be essential to ensure that the results of this study will inform clinical care. Variation in antenatal exposure, from consistent daily exposure to medical treatment of opioid use disorder to active use of illicit opioids, complicates neonatal opioid withdrawal and may impact an infant’s response to the approach to pharmacologic treatment. As such, we request a waiver of consent from the sIRB for this study to minimize the risk of biasing the sample towards stable maternal/infant dyads with less severe opioid dependency and comorbidities.

A cluster-randomized clinical trial may proceed without individual consent if Common Rule conditions for a waiver of consent are satisfied, and participants (or legally authorized representatives) are provided with a description of the study intervention to which their cluster has been randomized. As stated in Code of Federal Regulations [45 CFR 46.116 (d)], an sIRB may approve a consent procedure that does not include, or that alters, some or all of the elements of informed consent set forth in this section, or waive the requirements to obtain informed consent, provided the sIRB finds and documents that all of the following conditions are met:The research involves no more than minimal risk to the participants.The waiver or alteration will not adversely affect the rights and welfare of the participants.The research could not practicably be carried out without the waiver or alteration.Whenever appropriate, the study team will provide participants with additional pertinent information after participation.

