The justification for a waiver of informed consent from caregiver(s) for the previously outlined study objectives meets the above criteria as follows:The research involves no more than minimal risk to the participants.Both approaches to pharmacologic treatment (i.e., the symptom-based dosing approach and scheduled opioid taper approach) are currently used at sites across the country, and the optimal approach to pharmacologic treatment for infants with NOWS is unknown. The protocol study team has utilized recommendations from the AAP to define the primary outcome to further facilitate safe discharge practices for all infants with NOWS. Undertreatment and overtreatment will be minimized by the study parameters developed by the protocol study team and a DSMB will be engaged to identify any risk concerns throughout the study. The usual approach to management of NOWS is protocol-driven based upon a site level therapeutic approach. Dosing approach (symptom versus scheduled) is not decided at the level of the individual patient nor at the discretion of an individual practitioner. Thus, the role of removing individual physician discretion for specific infants, a commonly cited criteria against waiver of consent, is not an issue in NOWS in which dosing approach is determined at the facility level. This clinical trial will employ two widely accepted dosing approaches. In addition, the treatment of NOWS in the inpatient setting is extremely safe regardless of the opioid employed or dosing regimen. This is due to drug dosing that is directly tied to symptom scores every 4 h, signs of excess sedation being evident much before respiratory depression, and careful respiratory monitoring in an inpatient setting.The waiver or alteration will not adversely affect the rights and welfare of the participants.As the best pharmacologic management for infants with NOWS is unknown, there is no universally accepted standard approach, and both management strategies are currently being used at sites across the country. Therefore, participants receiving care via either approach to pharmacologic treatment should not have their rights and welfare adversely affected.The site research team could not practicably carry out this trial without the waiver or alteration.Recent clinical trials in NOWS for which individual patient consent to an altered therapeutic regimen (NCT04214834, 04104646) have encountered a patient consent rate of only 20–30% of those eligible. Though the patient parental characteristics of those who have declined participation cannot be collected in systematic fashion, clinical trialists at these sites have noted those declining tend to have more polysubstance abuse, have higher use of prescribed benzodiazepines and psychotropics, are less likely to be in an outpatient opioid use disorder program, and often have impulse control as part of a comorbid psychiatric diagnosis. Most of these factors have been linked to worse outcomes (as measured by symptom scores and length of treatment for infants). Large (for NOWS) randomized trials with individual level consent have all tended to have enrolled mothers with less of the risk factors listed above [22–24]. The feasibility and generalizability of this trial would be limited if obtaining informed consent were required. It is highly possible that infants with antenatal exposure to illicit or misused opioids may respond differently to symptom-based dosing approach than infants with antenatal exposure to medications for opioid use disorder (MOUD). The goal of this research is to identify a generalizable approach to pharmacologic treatment for infants with NOWS. Enrolling only a consented population will likely bias the study results towards infants born to women who are stable on MOUD and miss a high-risk sub-population of infants with NOWS. This could be particularly problematic in this trial where there may be variation in the response to treatment. Each study site will use the assigned approach to care for all infants with NOWS throughout the trial. Therefore, obtaining consent would not alter the care approach used for the infant. Thus, the benefits afforded by using a waiver of consent outweigh the risks to the infant receiving the same treatment.Whenever appropriate the study team will provide participants with additional pertinent information after participation.Throughout the study, the site study team will provide participants with additional pertinent information when appropriate. The site study team will (a) give to the caregiver(s) of all infants with NOWS who are cared for at the study site throughout the study and/or (b) post (as an enlarged copy) in appropriate location(s) readily visible to caregivers. This will fulfill the suggested framework [25] of participants being “provided with a detailed description of the study interventions to which their cluster has been randomized.”

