Assuming that the participants in OPTimize NOW are similar to those observed in INFORM NOW, sample size calculations of the primary endpoint given by time to medically ready for discharge were conducted under the following assumptions:In infants who were assessed and managed with FNAST:◦ The mean time to medically ready for discharge is approximately 16.50 in infants who are treated with a scheduled opioid taper approach.◦ Intra-class correlation coefficient in either arm is 0.15.◦ Over-dispersion parameter in either arm is 8.4.In infants who were assessed and managed with ESC:◦ The mean time to medically ready for discharge is approximately 10.50 in infants who are treated with a scheduled opioid taper approach.◦ Intra-class correlation coefficient in either arm is 0.15.◦ Over-dispersion parameter either arm is 5.5.

Under these assumptions, Table 5 shows that effect sizes that can be detected with 80% or 90% power in infants who are assessed and managed with ESC or FNAST using a total sample size of 480 participants (320 infants who are assessed and managed with ESC; 160 infants who are assessed and managed with FNAST) and assuming a two-sided significance level of 0.05. Specifically:In infants who are assessed and managed with ESC, a sample size of 320 will allow us to detect a relative rate in time to medically ready for discharge between infants who are treated with a symptom-based dosing approach versus infants who are treated with a scheduled opioid taper approach of 0.79 with 80% power and 0.76 with 90% power.In infants who are assessed and managed with FNAST, a sample size of 160 will allow us to detect a relative rate in time to medically ready for discharge between infants who are treated with a symptom-based dosing approach versus infants who are treated with a scheduled opioid taper approach of 0.71 with 80% power and 0.67 with 90% power.

**Table 5 Tab5:** Sample size calculations

Treatment approach	Number of sites per sequence	Number of infants with NOWS per site per period	Number of infants with NOWS	Power	Time to medically ready for discharge		Relative rate of days to medically ready for discharge between arms
					Scheduled opioid taper	Symptoms-based dosing	
ESC	8	10	320	80%	10.50	8.3	0.79
				90%		8.0	0.76
FNAST	4	10	160	80%	16.50	11.7	0.71
				90%		11.0	0.67

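### The primary model is valid, but its stated fixed effects leave out baseline data already collected; a short pre-specified covariate list would add precision and some protection against case-mix shifts

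*Protocol article*

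**What the plan says.** The Analysis plan section sets out one generalized linear mixed model for the objectives, fitted separately in ESC and FNAST infants. It states that "Each model will also include the following fixed effects" and lists dosing approach and the study period of birth. It adds: "Random effects for site will also be included in the model to account for within- and between-period intra-cluster correlation". Primary analysis of primary objective applies this model, with a negative binomial distribution and log link, to days until medically ready for discharge in ESC infants. The one supportive analysis named adds a dosing-by-period interaction.

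Among all enrolled infants lists sex, gestational age, birthweight and exposures during pregnancy among the data to be collected where available. Descriptive analyses uses baseline characteristics only for group comparisons.

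Waiver of consent for in-hospital participation treats exposure as important. It says of "Variation in antenatal exposure, from consistent daily exposure to medical treatment of opioid use disorder to active use of illicit opioids" that this complicates withdrawal and may affect response to treatment. It then describes mothers who decline trials (more polysubstance use, more benzodiazepines and psychotropics, less often in a treatment program) and says: "Most of these factors have been linked to worse outcomes", measured by symptom scores and length of treatment.

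On masking, Stratification, randomization, and blinding/masking says "the protocol study team, site PI, site study team, and participants will be unblinded to the assigned study intervention".

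**The concern.** Two things are at stake.

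- **Precision.** In a cluster crossover with exchangeable correlation, the site effect cancels from the within-site comparison. What limits power is the variation between infants within a site. Length of opioid treatment feeds directly into the primary endpoint, because readiness normally requires 48 hours since the last opioid dose. Factors that predict length of treatment should therefore explain some of that variation.
- **Case mix.** Infants are not individually randomized. They are identified from records after delivery, at sites that know their current allocation, and they enter on a staff-scored threshold (one FNAST score of 8 or more, or one ESC yes). The mix of infants at a site can therefore differ between its two periods. Neither the random site effect nor a common period term removes a shift that is particular to one site or related to the allocation.

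**Working it through.** **Inputs**, from Sample size considerations and Table 5:
- ESC: K = 16 sites, m = 10 infants per site per period, control mean 10.50 days, over-dispersion φ = 5.5, ICC 0.15.
- FNAST: K = 8, m = 10, control mean 16.50 days, φ = 8.4, ICC 0.15.
- Exchangeable correlation, t-distribution, "assuming a two-sided significance level of 0.05".

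**Step 1: reproduce the stated power without covariates.** For a two-period cross-sectional cluster crossover:

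Var(log RR) = (φ/μ0 + φ/μ1) × (1 − ICC) / (m × K), and power = T_df(|log RR|/SE − t_0.975,df).

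For ESC at RR 0.79, μ1 = 10.50 × 0.79 = 8.295. Then Var = (5.5/10.5 + 5.5/8.295) × 0.85/160 = 0.00631, SE = 0.0794, and |log 0.79|/SE = 0.2357/0.0794 = 2.97. With df = 2K − 3 = 29 the critical value is 2.045 and power is 81.8%.

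| Group | RR | Stated power | Recomputed |
|---|---|---|---|
| ESC | 0.79 | 80% | 81.8% |
| ESC | 0.76 | 90% | 91.0% |
| FNAST | 0.71 | 80% | 79.2% |
| FNAST | 0.67 | 90% | 89.0% |

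All four agree within 2 points, so the planned power does not rely on covariates.

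**Step 2: add covariates.** Multiply the variance by (1 − R²), where R² is the share of within-site variance explained by baseline covariates. The article gives no R², so the values below are assumptions. The equivalent unadjusted sample size is 320/(1 − R²).

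| Assumed R² | ESC power at RR 0.79, 29 df | Same, 14 df (K − 2) | ESC power at RR 0.85, 29 df | Equivalent unadjusted N |
|---|---|---|---|---|
| 0 | 81.8% | 78.8% | 51.7% | 320 |
| 0.05 | 83.7% | 80.9% | 53.8% | 337 |
| 0.10 | 85.6% | 82.9% | 56.1% | 356 |
| 0.20 | 89.4% | 87.0% | 61.3% | 400 |

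On the scale of days instead of the log scale, with 30 df, the power at RR 0.79 is 82%, 84%, 86% and 90%. FNAST power at RR 0.71 (13 df) goes from 79.2% to 81.2%, 83.3% and 87.3%. RR 0.85 is the small end of the 15% to 25% reduction that the article calls clinically meaningful.

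**Step 3: size of a case-mix shift (illustration only; all inputs assumed).** Suppose a factor multiplies time to readiness by g and has prevalence 40% under the taper and p1 under symptom-based dosing. With no true effect, the apparent RR is (1 + p1(g − 1)) / (1 + 0.40(g − 1)).
- g = 1.2, p1 = 35%: 1.07/1.08 = 0.99.
- g = 1.5, p1 = 30%: 1.15/1.20 = 0.96.
- g = 2.0, p1 = 25%: 1.25/1.40 = 0.89.

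The chance SD of such a prevalence difference with 160 infants per arm, taken as independent, is √(2 × 0.4 × 0.6/160) = 5.5 percentage points. Chance differences of this kind are already reflected in the standard error; only a systematic shift would be bias.

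**The case against.** The strongest reply is that nothing here is an error. Treatment, period and random site effects make a valid model for a cluster crossover, and the stated power is reproduced without covariates. **This stands.** A reader might infer that the primary analysis is biased or underpowered by its own standard; the article does not support that.

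The article also calls its analysis section brief and leaves detail to the SAP, which is not shown and could add covariates. **This stands in part.** The list of fixed effects is not called exhaustive, but it is a stated model, carried forward to the primary and interim analyses, and the suggestion addresses it as stated.

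A reader might also infer that protection against case-mix differences is given up altogether. **That goes too far.** Random site effects and separate ESC and FNAST models absorb stable differences between sites. The period term and the two sequences deal with shifts common to all sites. Enrolment under waiver of consent limits selective entry, and the Recruitment section says that starting clinical management is not affected by the intervention. Birth-time covariates also cannot fully correct selection that works through the staff-scored entry threshold.

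Two limits on the evidence also stand. The article says that most of the listed maternal factors are linked to worse outcomes, without saying which, and nowhere calls gestational age or sex prognostic. And the gain depends on an assumed R²: at 0.10 or below it is at most about 4 power points.

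**Conclusion.** The point holds as an improvement in efficiency and robustness, not as a defect that invalidates the plan. Using data already collected would raise ESC power at RR 0.79 from about 82% to about 84% to 90%, conditional on an assumed R² of 0.05 to 0.20; with 14 degrees of freedom the change is from 79% to between 81% and 87%. At RR 0.85 the same assumptions move power from about 52% to between 54% and 61%, so adjustment helps there but does not make that effect reliably detectable. Protection against case-mix shifts would be partial: it covers measured factors only, and matters for shifts that are site-specific or related to allocation. The article gives no evidence that such shifts have occurred.

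**What to change.** Add a short pre-specified covariate list to the primary ESC model and to the FNAST model of the same endpoint: for example gestational age, sex, and type of antenatal opioid exposure with a polysubstance indicator. Keep the unadjusted model as a sensitivity analysis.

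- **Timing.** Interim analysis of efficacy data uses the primary model at about 50% of infants. Fix the list without sight of outcomes by arm and before that test, so that interim and final tests use the same model. Enrolment was expected to end in April 2025, so the interim may already have taken place; the article does not say. If it was run unadjusted, leave the primary model alone and add the adjusted model as a named sensitivity analysis.
- **Choice of variables.** Use only covariates that allocation cannot affect. Exposure can be established by infant toxicology during the stay, so state how exposure type is derived. Do not adjust for withdrawal scores or treatment.
- **Missing data.** Baseline data are collected where available. State the method for missing maternal data in advance. A missing category is a weak choice if case mix is not balanced.
- **Scope.** Do not force the full list into the other secondary models. Log-link binary models can fail to converge, and the dose-count model covers only treated infants, split by drug: about 39.1% × 320 = 125 ESC and 78.8% × 160 = 126 FNAST infants before that split, at the treatment rates quoted from the earlier data.
- **Adjusted means.** State how mean days per arm and their difference are averaged over the covariates.

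The cost is a few lines of text, a few extra parameters and some missing maternal data. No new data collection is needed.

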#### Primary analysis of primary objective

Using the model outlined in the Analysis plan section, the number of days from birth until the participant meets criteria for medically ready for discharge will be analyzed in all infants in the ITT population who are assessed and managed with ESC using a GLMM with a negative binomial distribution and log link function. This model will be used to estimate the following quantities (and corresponding 95% CIs):Adjusted mean number of days until medically ready for discharge in infants managed for NOWS with a symptom-based dosing approachAdjusted mean number of days until medically ready for discharge in infants managed for NOWS with a scheduled opioid taper approachDifference in adjusted mean number of days until medically ready for discharge between infants managed for NOWS with a symptom-based dosing approach and infants who managed for NOWS with a scheduled opioid taper approachAdjusted relative rate (RR) of days until medically ready for discharge comparing infants managed for NOWS with a symptom-based dosing approach to infants managed for NOWS with a scheduled opioid taper approach

#### Supportive analyses of the primary objective

To investigate if the intervention effect (i.e., symptom-based dosing approach versus scheduled opioid taper approach) is modified by the study period in which the participant was born (study period 1 or 2), a two-way interaction between dosing approach and study period will be added to the model described in the Primary analysis of primary objective section. Further details regarding the interpretation of the fitted model will be provided in the SAP.

